### Discontinuation criteria – suspension of intervention

Participants will be withdrawn from the study if one of the following occurs:

Major amputation (ankle, leg, or thigh) of the treated limb.Loss of follow-up.Clinical worsening (at the discretion of the investigator).Active ulcer infection.Unfit conditions to be subjected to the cellular therapy procedure within one month after the set date for the procedure.

If a participant’s intervention is discontinued, they will be followed up and encouraged to return for scheduled visits.

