### Discontinuation criteria – participant withdraw

The participant has the right to withdraw from the study at any time, either of their own will or by decision of the researcher, due to safety issues or poor adherence to follow-up. If a participant communicates their withdrawal from the study or revokes their consent, this communication will be documented by the researcher and no data will be collected.

If, upon withdrawal from the study, the participant has an ongoing adverse event or unresolved clinical or laboratory abnormality, the researcher will offer follow-up until the event is resolved or stabilized.

The study monitoring team will maintain regular contact with participants through telephone calls to encourage them to attend their medical reassessment appointments. Additionally, the research team will be available to address any questions or concerns from participants at any time.

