### Primary outcomes

#### Safety.

Absence of major amputations (ankle, leg, or thigh).EfficacyTotal ulcer epithelialization and limb salvage rate (non-occurrence of a major amputation).

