### Data collection plan

The study will be conducted at a single center, which will serve as the coordinating hub and be responsible for all stages of the RCT.

Verification and authenticity of the data quality entered into the electronic clinical record and printed documents will be carried out by the research team at our Clinical Research Unit (UPECLIN) according to the monitoring plan, during the execution and at the end of the clinical study.

To prevent data loss, we will develop standardized data collection forms and monitor the collected data regularly. Patients will be contacted frequently by telephone or social media, with updates often provided during these contacts. The appropriate clinical support will be offered to patients to minimize losses. Disease progression resulting in death or amputations will be defined as endpoints and will not be classified as data loss.

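### The withdrawal rule is triggered by the trial's own outcomes and conflicts with its follow-up rule, so healing and later outcomes may be lost; the role of death in limb salvage is left open

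*Protocol article*

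**What the plan says.** All references are to the Protocol article.

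- **Discontinuation criteria – suspension of intervention.** The heading speaks of the intervention, but the operative sentence is "Participants will be withdrawn from the study if one of the following occurs". The first four triggers read: "Major amputation (ankle, leg, or thigh) of the treated limb.Loss of follow-up.Clinical worsening (at the discretion of the investigator).Active ulcer infection". The fifth is being unfit for the cell procedure within a month of its set date. The section then closes: "If a participant’s intervention is discontinued, they will be followed up and encouraged to return for scheduled visits".
- **Primary outcomes.** Absence of major amputation is the primary safety outcome. Primary efficacy is complete epithelialisation together with "limb salvage rate (non-occurrence of a major amputation" (the closing bracket follows in the source).
- **Secondary outcomes, Safety.** Death is listed here, as are local infection, increased pain and a larger ulcer.
- **Data collection plan.** "Disease progression resulting in death or amputations will be defined as endpoints and will not be classified as data loss".
- **Sample size.** The analysis is to be by intention to treat.
- **Sample size and Statistics, closing paragraph.** Where only part of the data is missing, it may be left out. Interpolation is considered above 10% missing. Multiple imputation is used for larger amounts below 50%.

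**The concern.** A participant who meets one of these triggers has, in most cases, just had a bad outcome or is at high risk of one. Someone whose ulcer is infected or worsening is less likely to heal. If such people leave the study, their healing status, later limb status and later adverse events are not observed, and what remains is a selected group.

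Two features could make the loss differ by arm. The trial is open, and worsening is a matter of judgement for an investigator who knows the allocation. The external evaluators described under Blinding are masked, but they cannot read images that were never taken. The trigger about fitness for the cell procedure also applies, on its face, to Group 1 only.

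The role of death is a related gap. It is a secondary safety outcome and is absent from the definition of limb salvage. The Data collection plan calls it an endpoint without saying of which outcome. In a population that the Introduction describes as having high rates of amputation and death, this affects how a primary outcome is read.

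**Working it through.** **Inputs.** Healing of 75% and 30%, two-sided 5%, 80% power and 20 per group come from Sample size. The documents give no expected rates of amputation, death, infection or withdrawal, so every event count below is an assumption.

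1. **The plan's own figure.** With pooled variance, n = [1.96·√(2·0.525·0.475) + 0.8416·√(0.75·0.25 + 0.30·0.70)]² / 0.45² = (1.384 + 0.531)² / 0.2025 ≈ 18.1, so 19 per group. The plan's 20 reproduces, with power 84.1% by the same normal approximation. The sample size is not in question here. No allowance for lost outcomes is stated.

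2. **The sections side by side.**

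| Event | Withdrawal trigger | Also an outcome | Endpoint in Data collection plan |
|---|---|---|---|
| Major amputation | Yes | Primary safety and part of primary efficacy | Yes |
| Active ulcer infection | Yes | Secondary safety | No |
| Clinical worsening | Yes, by judgement | Overlaps secondary safety (pain, ulcer size) | No |
| Death | Not listed | Secondary safety; outside the limb salvage definition | Yes, but of which outcome is not said |

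3. **Healing if unhealed participants are dropped.** Take 6 healed of 20 and drop d unhealed, giving 6/(20 − d):
   - d = 0: 30%
   - d = 2: 6/18 = 33.3%
   - d = 4: 6/16 = 37.5%
   - d = 6: 6/14 = 42.9%

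4. **Effect on the comparison.** This depends on who is lost. Start from 15/20 v 6/20, a difference of 45 points and an odds ratio of (15/5)/(6/14) = 7. If 40% of non-healers are dropped in each arm, the expected figures are 15/(15 + 0.6·5) = 15/18 = 83.3% and 6/(6 + 0.6·14) = 6/14.4 = 41.7%. The difference is then 41.7 points and the odds ratio is still (15/3)/(6/8.4) = 7. Loss at the same rate among non-healers therefore inflates both rates without favouring either arm on the odds scale.

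5. **Unequal loss.** Assume true healing of 30% in both arms of 20. Each non-healer in one arm is dropped with probability q, and none in the other. The exact probability of a two-sided Fisher p ≤ 0.05 in favour of the arm that loses patients is:
   - q = 0: 1.2%
   - q = 20%: 3.6%
   - q = 40%: 7.7%

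   The nominal level is 2.5% per side.

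6. **Deaths with the limb intact.** Assume 4 amputations in 20. Limb salvage as defined is (20 − 4)/20 = 80% whatever the number of such deaths. Amputation-free survival is (20 − 4 − d)/20, which is 80%, 70% and 60% for d = 0, 2 and 4.

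**The case against.** The strongest reply is that no text removes withdrawn participants from the denominator. Intention to treat is stated, amputation and death are declared endpoints, and the closing sentence of the section keeps people in follow-up. An amputation has already been observed when it triggers withdrawal. If those statements govern, the bias from amputation is zero. This stands, and it is why the consequence is conditional. It does not settle infection or worsening: neither is named in the Data collection plan, and an intention-to-treat label cannot supply a healing status that was not recorded.

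The participant-withdrawal section offers follow-up of an ongoing adverse event until it resolves or stabilises. That helps in part, but it follows the event and does not secure ulcer and limb assessment to the closing visit. The statement there that "this communication will be documented by the researcher and no data will be collected" concerns participants who withdraw themselves or revoke consent, so it should not be read as covering investigator-led withdrawal.

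The missing-data text does not always permit omission. Four missing of 40 is 10%, which is not above the threshold for interpolation; larger losses would call for interpolation or imputation. Interpolation, however, needs a later observation, which a withdrawn participant would not have.

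Four stronger readings are tempting, and the documents do not support them:

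- **Withdrawal after the single cell application can mean only loss of observation.** The bio-dressing stays on for 7 days, and daily hydrogel care continues in both groups, so there is still an intervention to suspend.
- **A participant withdrawn for worsening before any amputation is scored as a salvaged limb.** No scoring rule for such a participant is given.
- **Dropping four non-healers per group shows the effect of balanced loss.** It turns 75% v 30% into 15/16 = 94% v 37.5%, but it removes 4/5 = 80% of Group 1 non-healers and 4/14 = 29% of Group 2 non-healers.
- **Limb salvage must be replaced as a primary outcome.** Its definition is explicit and death is reported separately. Replacing it would be a redesign on which statisticians may differ.

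Detailed scoring rules may also sit in a fuller document. The contradiction, however, is in the text shown.

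**Conclusion.** The point holds in conditional form. The section on suspension of intervention contradicts itself and sits badly with intention to treat, and its triggers overlap the outcomes. If staff follow the withdrawal sentence, healing status, later limb status and later safety data after infection or worsening can be lost, and unequal loss can bias the comparison. A reader might infer that the results will favour whichever arm loses its sickest patients. The documents do not support that, because which instruction prevails and how losses fall by arm are both unknown.

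On assumed counts, four dropped non-healers move a 30% healing rate to 37.5%. One-sided loss of 40% of non-healers raises that arm's false-win probability from 1.2% to 7.7%. Equal rates of loss leave the odds ratio unchanged.

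The death point holds on a literal reading: up to 20 percentage points separate limb salvage from amputation-free survival in the assumed examples.

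**What to change.** Reconcile the suspension section with Sample size and the Data collection plan, so that major amputation, ulcer infection and clinical worsening do not end outcome assessment. Every randomised participant stays under scheduled assessment to the closing visit unless consent for data collection is withdrawn. When treatment itself is stopped is not addressed; those passages only need to be made consistent.

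For the analysis:

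- Include all randomised participants.
- Count major amputation or death before healing as not healed.
- For participants with infection or worsening, use the observed final healing status, and count them as not healed if it was not observed.
- Keep limb salvage as defined, but report amputation-free survival (major amputation or death) and its components beside it, so that deaths are not read as successes.

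The cost is amendment wording and its submission; the visits are already in the Participant timeline. Healing and limb figures may be less favourable, and scoring unobserved healing as failure is itself an assumption that lowers the rate most in the arm with more missing assessments.

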### Participant replacement

Participants excluded during the screening period – which corresponds to the interval between the initial assessment and first reassessment of the arterial ulcer, before receiving cellular therapy – may be replaced by another participant. The new participant will be allocated to the same randomization position as the excluded participant to preserve the balance between treatment groups and the integrity of the randomization. The eligibility of substitutes will be verified according to the same inclusion and exclusion criteria established in the protocol.

During this phase, participants with unstable clinical conditions will be monitored for up to one month. After this period, clinical reassessment will be carried out. If the underlying conditions are resolved, they may be reevaluated for inclusion (Fig 1).

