#### Group 1.

Cell Therapy Treatment Group: Participants will receive expanded ASC treatment. The participant will undergo a surgical debridement procedure of the ulcer so that it is in its best condition (Visit 1). Subsequently, the participant will receive an ASC application via perilesional subcutaneous injections and a bio-dressing produced by the study team, also containing ASCs (the dressing containing ASC will remain in contact with the ulcer for 7 days in a single session). After removing the biological dressing, the participant will receive local care for the ulcer with a topical hydrogel dressing, dry gauze, and a crepe bandage, changed at least once a day.

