#### Grupo 2.

Control Group: Participants will receive local ulcer care. The participant will undergo a surgical debridement procedure of the ulcer so that it is in its best condition (Visit 1). Subsequently, the participant will receive local care for the ulcer with a topical hydrogel dressing, dry gauze, and a crepe bandage, changed at least once a day.

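### One reason for withdrawal from the study can be met only in Group 1, after allocation is known, and conflicts with intention to treat and with the section's own follow-up sentence

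*Protocol article*

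**What the plan says.** The section on suspension of intervention opens its list with "Participants will be withdrawn from the study if one of the following occurs". There are five reasons: major amputation of the treated limb, loss to follow-up, clinical worsening as judged by the investigator, active ulcer infection, and "Unfit conditions to be subjected to the cellular therapy procedure within one month after the set date for the procedure". The section closes with "If a participant’s intervention is discontinued, they will be followed up and encouraged to return for scheduled visits".

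The arms are described separately. For Group 1: "Cell Therapy Treatment Group: Participants will receive expanded ASC treatment". For Group 2: "Control Group: Participants will receive local ulcer care". Both arms have a surgical debridement at Visit 1, but only Group 1 has the cell application, which the Intervention section places under locoregional or general anaesthesia.

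Four other places bear on the point:
- Sample size: the study is to be analysed by intention to treat.
- Randomization: the team learns the allocation at adipose tissue collection.
- Abstract, Methods: the cells are expanded for 14–21 days before application.
- Participant replacement: someone excluded during screening, a period described as lying before cell therapy, may be replaced by a new participant in the same randomization position. In that phase "participants with unstable clinical conditions will be monitored for up to one month", and "If the underlying conditions are resolved, they may be reevaluated for inclusion".

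**The concern.** Four of the five reasons can arise in either arm. The fifth cannot, because a control has no cell procedure for which to be unfit. Allocation is open by the time the procedure is scheduled, so an unblinded team applies the criterion to one arm only.

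It probably also selects on prognosis. Patients judged unfit for a procedure under anaesthesia are likely to do worse on limb, ulcer and survival. The documents do not say so, but it is a reasonable assumption. If they leave Group 1 while comparable controls stay, the arms are no longer the groups that were randomized, and the cell arm can look better even if the cells do nothing. A fitter substitute in the vacated position would have a similar effect.

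The text does not settle whether this happens. Withdrawal from the study points one way, and intention to treat and the follow-up sentence point the other.

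**Working it through.** **1. The plan's own figure.** With 75% against 30% healing, two-sided 5%, 80% power and pooled variance:

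n = [1.96·√(2·0.525·0.475) + 0.8416·√(0.75·0.25 + 0.30·0.70)]² / 0.45² = (1.384 + 0.531)² / 0.2025 ≈ 18.1, so 19 per group.

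The stated 20 per group is consistent with this and gives 84.1% power by the normal approximation. The sample size is not in question here. No allowance for dropout is stated.

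**2. Can the criterion act after allocation is known?** Allocation opens at tissue collection. Application follows 14–21 days later. The criterion then runs for up to one month from the set procedure date. So it can.

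**3. Can a control meet it?** The criterion names the cell procedure, which the Group 1, Group 2 and Intervention sections give to Group 1 only. So a control cannot.

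**4. What happens to the data?** The list says withdrawal from the study. The closing sentence says follow-up when the intervention is discontinued, and it is unclear whether that covers someone in whom the cell application was never started. The Sample size section says intention to treat. These cannot all govern the same participant.

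**5. Size if these participants were dropped from the analysis despite intention to treat.** Inputs:
- 30% healing, the protocol's control rate, taken as true in both arms (no treatment effect): 6 of 20.
- 20% major amputation in both arms (assumed): 4 of 20.
- u = 2 to 4 unfit participants in Group 1 (assumed).
- Among them, healing h = 0 to 10% and amputation a = 40 to 50% (assumed).

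Remaining Group 1 healing = (6 − u·h)/(20 − u). Remaining Group 1 amputation = (4 − u·a)/(20 − u).

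| u | h | Healing | a | Amputation |
|---|---|---|---|---|
| 2 | 10% | 5.8/18 = 32.2% | 40% | 3.2/18 = 17.8% |
| 2 | 0% | 6/18 = 33.3% | 50% | 3/18 = 16.7% |
| 4 | 10% | 5.6/16 = 35.0% | 40% | 2.4/16 = 15.0% |
| 4 | 0% | 6/16 = 37.5% | 50% | 2/16 = 12.5% |

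Against 30% and 20% in controls, the spurious benefit is 2.2 to 7.5 points on each outcome.

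A wider range for healing takes an unfit share f of 10 to 30% and healing of 0 to 20% among them. Then (0.30 − f·h)/(1 − f) runs from (0.30 − 0.02)/0.9 = 31.1% to 0.30/0.7 = 42.9%, a gain of about 1 to 13 points.

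**6. Price of keeping them in.** Suppose the planned 75% holds for those treated and all k unfit participants count as not healed, which is the worst case. The Group 1 rate is then 0.75·(20 − k)/20: 67.5% for k = 2 and 60% for k = 4. Power by the normal approximation is 67% and 48%, against 84.1% with none unfit.

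**The case against.** The case on the other side has four parts.

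*Protections already in the text.* The section is headed as suspension of intervention, it promises follow-up, and the analysis is by intention to treat. The Data collection plan adds that death and amputation count as endpoints and not as data loss. If these govern, the participants stay in and no bias arises. This stands as a reason not to treat their removal from the analysis as settled. It does not remove the conflict with withdrawal from the study.

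*Frail controls can leave too.* Clinical worsening and active ulcer infection apply to both arms. This stands: a reader might infer that frail patients leave one arm only, but that is true of this criterion and not of the whole list. The one-arm criterion still comes on top of the shared ones.

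*Re-entry.* A reader might infer that the replacement section re-admits the patient whom the suspension section withdraws, and that he could be allocated twice. The documents do not say so. The two one-month rules start from different points and can be read in sequence: reconsider if the condition resolves, withdraw if it does not. The vacated position goes to a new participant, and nothing gives a returning patient a second position. The text does not rule one out, but it does not provide for one. The figure cited there is not shown, and the full protocol, which may say more, is not at hand.

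*The size rests on assumptions.* Only the 30% healing rate comes from the protocol. The direction follows from assuming that unfit patients do worse, and 2 to 8 points is small beside the planned 45-point difference. All of this stands.

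**Conclusion.** The concern holds as a conflict in the text with a possible bias. One reason for withdrawal from the study can be met only in Group 1, can act after allocation is open, and does not fit with intention to treat or with the section's own follow-up sentence. The replacement rule may add to this by filling the vacated position with someone else.

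The bias arises only if these participants are dropped or replaced despite intention to treat. In the case of dropping, it is about 2 to 8 points on healing and on major amputation, given no treatment effect, 2 to 4 of 20 unfit, and a worse prognosis among them. The documents give no rate of unfitness, so this is an illustration and not an estimate. Re-admission and double allocation are not supported as findings; they are at most possibilities that one sentence would close. The text should be corrected, ideally before recruitment starts.

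**What to change.** Reconcile the Participant replacement, Sample size and suspension-of-intervention sections so that they say one thing:

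- A Group 1 participant who does not receive the cell procedure after allocation has been opened is recorded as *assigned procedure not given*. He is not withdrawn from the study, and not replaced, for that reason.
- He stays on the scheduled visits and is counted in Group 1 for all primary and safety outcomes. The Participant timeline section counts reassessment days from randomization, which gives a usable starting point for someone never treated.
- Anyone re-evaluated after allocation has been opened keeps the original number and arm.

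Whether and when the procedure is done stays with the investigators; the change concerns only study status, follow-up and counting.

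The cost is wording in these sections and visits that are already scheduled. The downside is dilution: untreated Group 1 participants pull the estimated effect down and lower power, in the worst case above to 67% with two such participants and 48% with four. That is the price of the intention-to-treat analysis the protocol already promises, and the sponsor should know it before recruiting.

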### Primary outcomes

#### Safety.

Absence of major amputations (ankle, leg, or thigh).EfficacyTotal ulcer epithelialization and limb salvage rate (non-occurrence of a major amputation).

### Secondary outcomes

#### 
Safety.

Death, acute myocardial infarction (AMI), cerebrovascular accident (CVA), thromboembolic events such as deep vein thrombosis (DVT) and pulmonary embolism (PE), systemic infectious condition, cancer, local infections, bleeding, worsening pain and enlargement of the ulcer area.Any adverse event not mentioned in the previous items or negative and clinically significant changes in laboratory parameters (glycemia, glycated hemoglobin, HDL, LDL, total cholesterol, triglycerides, leukogram, hematocrit, uric acid, urea, creatinine, CRP, sodium, potassium, alkaline phosphatase (ALP), alanine transaminase (ALT), aspartate transferase (AST), gamma-glutamyl transferase (GGT), bilirubin, total protein, albumin, prothrombin time (PT), partial thromboplastin time (PTT)) and tissue histological analysis.

